#### Logbook

3.2.5

To document the study process and decisions made throughout, researcher MH makes notes in a logbook. This logbook contains notes of all attended meetings with TANM’s coordinating organizations as well as feedback meetings held with the ambassadors and representatives from the coordinating organizations. The notes capture key decisions during the study and intervention process, feedback received by the coordinating organizations and ambassadors, and personal reflections of the researcher. As such, these notes will provide context for interpreting the findings and aligning them with the program theory, contributing to a nuanced interpretation of the results and supporting the data triangulation process in Phase 3. The template of the logbook has been added to Supplementary material IV.

### Phase 3: data analysis and theory refinement

3.3

The analysis process comprises method-specific analyses for each type of data collected, followed by an integrative synthesis to triangulate our findings and refine the initial program theory. Below, we describe each type of analyses, followed by a description of how we will triangulate the data and refine the program theory.

#### Qualitative data: interviews and observations

3.3.1

Audio recordings of interviews will be transcribed verbatim, and observation schemes, completed during fieldwork, will be digitalized. Additionally, the open-ended question from the post-intervention questionnaire will be transcribed and analyzed as part of the qualitative data.

Thematic analysis will be conducted using both deductive and inductive approaches. Deductive analysis is guided by the initial program theory, with a coding framework structured around the concepts within our CMO-configurations (see Figure 3). At the same time, inductive analysis allows new themes and mechanisms to emerge within the predefined categories of context, mechanisms, and outcomes (41).

The analysis will follow Braun and Clarke’s (42) six-step framework: starting with familiarization with the data through repeated reading, followed by systemic coding, theme development and refinement. Coding will be conducted in Atlas.ti [Version 24; (43)].

#### Quantitative data: questionnaire

3.3.2

Quantitative data from the post-intervention questionnaire will be analyzed using SPSS [Version 29.0.0.0; (44)] to examine differences across intervention groups and assess the potential influence of contextual factors on perceived mechanisms and outcomes. Based on the initial program theory, we expect differences between groups (i.e., whether participants knew each other or their ambassador beforehand and the cultural homogeneity of the group), which may influence social support and group dynamics (such as sharing personal experiences with caregiving and/or mental illness and perceptions of taboo). To explore these potential mechanisms within our program theory, we will conduct crosstabulations of these independent and dependent variables, supplemented by chi-square tests to assess the statistical significance of observed differences.

Based on previous studies on peer education with migrants [e.g., (45, 46)], we estimate an effect size of 0.4. Using a power analysis in R (47) with the pwr package (48) we expect to need around 60 completed surveys to achieve sufficient power. Given that we anticipate collecting around 8–12 questionnaires per intervention group, totalling approximately 80–100 questionnaires, we expect to have adequate power for our questionnaire analysis.

Missing data will be included in the analyses as is, unless responses to other questions suggest that the omission can be reasonably filled in based on available information. In such cases, missing responses may be assessed using other relevant data from the same participant. All decisions regarding missing data will be reported transparently in the final analysis.

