2b	Interactions with representatives from care organizations during peer education sessions help migrant families overcome distrust and unfamiliarity. These foster increased trust and willingness to seek help from the Dutch healthcare system.	Interviews, observations
3a	Peer education and informational support enhance migrant families’ awareness of available healthcare options. This improves accessibility and fostering better utilization of support services.	Interviews, observations
3b	Ambassadors identify informal caregivers and refer them for tailored follow-up support. This follow-up equips them with the skills and support needed to manage caregiving responsibilities and burdens effectively.	Interviews
4a	Trusted peers (i.e., ambassadors) with strong community ties recruit participants and create a safe, reassuring environment. This increases participation in mental health support programs, despite stigma or mistrust.	Interviews, questionnaire
4b	Participants share knowledge and personal stories with their intervention groups and with their communities. This reduces stigma and spreading understanding about mental health and caregiving.	Interviews, questionnaire, observations
4c	From an organizational perspective, flexibility in adapting training content, communication, and support to cultural and practical needs is needed. This enables inclusive participation and enhances access to information and care for migrant families.	Interviews, observations

**Table 2 tab2:** Overview of data collection methods, CMO-configurations, sample size, frequency, and purpose in realist evaluation.

Method	CMO-configuration	Sample size/frequency	Purpose in realist evaluation
Interviews with ambassadors, semi-structured	1a, 1b, 2a, 2b, 3a, 3b, 4a, 4b, 4c	*n* = 10	Understanding ambassador’s perspectives on CMO-relationships
Interviews with participants, semi-structured	1a, 1b, 2a, 2b, 3a, 3b, 4a, 4b, 4c	2 per ambassador, total *n* = 20	Exploring firsthand experiences of short-term outcomes and factors that influenced these changes
Observations	1a, 1b, 2a, 2b, 3a, 4b, 4c	1–2 per group	Capturing real-time behaviors of ambassadors and participants and context
Post-intervention questionnaire	1a, 1b, 4a, 4b	Approx. *n* = 100 (10 ambassadors, ~10 participants each, varying)	Identifying patterns and insights from participants to support interpretation of qualitative findings

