Group composition	5	Did you know the other participants before the start of the sessions? Answer categories: yes/no. If yes, where from? Answer categories: previous training, church, (volunteer) work, common friends or acquaintances, neighborhood or district.
Social support mechanisms	5	Can you talk to the other group members when you do not feel well or need support? Answer categories: yes/sometimes/no
Mental health taboos and group dynamics	4	Did your group members talk about their experiences with caring for a loved one? Answer categories: yes/sometimes/no

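### Chi-square tests in section 3.3.2 treat 80–100 participants from about 10 ambassador-led groups as independent, so p-values for group-level context will be too small if answers correlate within groups

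*Protocol article*

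**What the plan says.** Section 3.3.2 names the context factors and treats them as contrasts between groups: "we expect differences between groups (i.e., whether participants knew each other or their ambassador beforehand and the cultural homogeneity of the group"). They are related to outcomes at the level of support and interaction, "which may influence social support and group dynamics (such as sharing personal experiences with caregiving and/or mental illness and perceptions of taboo"). The test is fixed in the same paragraph: "we will conduct crosstabulations of these independent and dependent variables, supplemented by chi-square tests to assess the statistical significance of observed differences".

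Table 2 gives the sampling structure as "10 ambassadors, ~10 participants each, varying". Section 3.3.2 expects 8–12 questionnaires per group and about 80–100 in all. It sets the need at around 60 surveys for an effect size of 0.4 and concludes that power is adequate.

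Table 3 shows both kinds of item. One context item is put to each person: "Did you know the other participants before the start of the sessions? Answer categories: yes/no". One outcome item asks every member about the same group: "Did your group members talk about their experiences with caring for a loved one? Answer categories: yes/sometimes/no".

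According to section 2, ambassadors recruit their own participants and lead the sessions in the group's main language. Section 3.2.4 says that forms are completed individually. It also says that, where Dutch is not understood, one assistant translates each question aloud to the whole group. The article mentions no adjustment for group, in the tests or in the sample size.

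**The concern.** The Pearson chi-square test takes each respondent as an independent observation. Here the members of a group share an ambassador, a language, the same sessions and sometimes the same oral translation, and some items ask them about the same group. Their answers are therefore likely to resemble each other more than answers from different groups.

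The damage depends on the exposure. Cultural homogeneity does not vary within a group, so any chance difference between the groups on either side of the split counts as if 80–100 people had shown it independently. Acquaintance can vary within a group, but recruitment through one ambassador makes it likely to cluster.

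At stake is the weight given to a significant context effect in the synthesis matrix (section 3.3.3), and from there in refining the configurations that the questionnaire informs (1a, 1b, 4a and 4b in Table 2). The power statement rests on the same independence assumption.

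**Working it through.** **1. The plan's own figure.** Inputs from section 3.3.2: effect size 0.4, around 60 surveys. Assumed because not stated: the effect size is Cohen's w, alpha is 0.05 and power is 0.80. A yes/no factor against a yes/sometimes/no answer is a 2×3 table with df = 2. Power comes from the noncentral chi-square distribution with noncentrality N × w² = N × 0.16. Solving for 80% power gives N = 60.2, so 61. The plan's figure is reproduced (df = 1 gives 50, df = 3 gives 69). The formula assumes independent respondents.

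**2. Type I error, latent-scale ICC.** Setting: 10 groups of 10, three-level answer with probabilities 0.5/0.3/0.2 cut from a normal variable with a group component, no true effect, ordinary chi-square test at 5%. The group-level factor is split 5 v 5. The partly clustered factor has 90% prevalence in five groups and 30% in the other five. The ICCs are assumptions.

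| Latent ICC | Group-level factor | Partly clustered factor | Factor that does not cluster |
|---|---|---|---|
| 0 | 5% | 5% | 5% |
| 0.05 | 8% | 6% | 5% |
| 0.1 | 10–11% | 7% | 5% |
| 0.2 | 18–19% | 9–10% | 5% |

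**3. Cross-check, ICC on the observed categories.** The design effect is DE = 1 + (m − 1) × ICC, with m = 10. With df = 2 the chi-square tail has a closed form, so the approximate true error for a group-level factor is 0.05^(1/DE).

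- ICC 0.05: DE = 1 + 9 × 0.05 = 1.45, and 0.05^(1/1.45) = 12.7% (simulated 12.1%).
- ICC 0.10: DE = 1.90, and 0.05^(1/1.90) = 20.7% (simulated 21.9%).

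These rates exceed those in step 2 at the same nominal ICC because the scale differs: a correlation on the latent scale is weaker once the answer is cut into three categories. The two sets should not be mixed.

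**4. The power statement for a group-level factor.** Required N = 61 × DE. The effective number is the expected total divided by DE. ICCs are on the observed scale.

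| ICC | DE (m = 10) | Required N | 100 surveys are worth | Power, 100 surveys | Power, 80 surveys (m = 8) |
|---|---|---|---|---|---|
| 0 | 1.00 | 61 | 100 | 0.96 | 0.90 |
| 0.02 | 1.18 | 72 | 85 | 0.92 | 0.86 |
| 0.05 | 1.45 | 89 | 69 | 0.85 | 0.79 |
| 0.10 | 1.90 | 116 | 53 | 0.74 | 0.69 |
| 0.20 | 2.80 | 171 | 36 | 0.56 | 0.53 |

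With 100 surveys, 80% power holds only while the ICC stays below roughly 0.07. These figures use a large-sample approximation; a test with only 10 groups would do somewhat worse.

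**5. What a group-level test can show.** An exact permutation test on 10 group values has as many arrangements as there are ways to split the groups. A 9/1 split has 10, so the smallest p is 1/10 = 0.10 and 5% cannot be reached. An 8/2 split has 45, so the smallest p is 1/45 = 0.022. The article does not say how the groups will divide on homogeneity.

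**The case against.** The strongest reply is that little depends on these p-values. Section 3.2.4 calls the questionnaire component exploratory, Table 2 gives it the role of supporting interpretation of qualitative findings, and it covers four of nine configurations. The tests supplement descriptive tables, and section 4.1 says that the study cannot establish causality. This stands, and it lowers the severity. It does not make the tests valid, because section 3.3.2 still uses them to judge significance and claims enough power for them.

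Three stronger readings are tempting, and the article does not support them.

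- A reader might infer that every p-value will be too small. That depends on an unknown ICC and on how far the exposure clusters. For an exposure that does not cluster, the error stays near 5% at every ICC tried.
- A reader might infer that members' answers must agree because they describe a shared event. Forms are completed individually, and the support item shown in Table 3 is personal. Correlation is likely, but its size is not known.
- A reader might infer that one unusual group could by itself confirm a configuration. Section 3.3.3 requires findings from different sources to align and has discrepancies explored. All four questionnaire-linked configurations also have interviews, and three have observations. A spurious result can add weight but cannot confirm alone.

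**Conclusion.** The point holds, most firmly for cultural homogeneity. There the independent units number about 10, and the ordinary chi-square test is anti-conservative for any positive within-group correlation. For prior acquaintance the same fault is milder and conditional on clustering. The sizes in the working rest on assumed ICCs, 10 equal groups of 10, a 5 v 5 split and one set of answer probabilities; the direction for a group-level factor needs only an ICC above zero. The sample size of around 60 and the claim of adequate power hold only for independent respondents. Because the component is exploratory and triangulated, this should be fixed before analysis, but it does not threaten the study's main qualitative conclusions.

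**What to change.** - **Crosstabulations:** keep them as description, and show results by group.
- **Group-level factors (cultural homogeneity):** drop the participant-level chi-square p-values. Either report these factors descriptively, which is the simplest choice for an exploratory component, or reduce each group to one value and use an exact permutation test where the split of the 10 groups allows p < 0.05.
- **Acquaintance items:** use an ordinal model or generalized estimating equations that account for intervention group, with a small-sample correction for about 10 clusters. A Cochran–Mantel–Haenszel test stratified by group addresses only the within-group association and should be labelled so. It discards the contrast between groups that section 3.3.2 sets out to examine, and groups in which everyone or no one knew the others contribute nothing to it.
- **Power statement:** say that around 60 surveys assumes independent respondents, and restate it with a design effect over a range of assumed ICCs. Report the observed ICCs.

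The cost is a rewrite of the analysis and power paragraphs. No new data are needed, provided each form is marked with its group, which is easy because forms are handed out at the group's own session. The downside is wider intervals and fewer significant results.

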Once selected, ambassadors receive specialized training, covering three main areas: (1) basic knowledge of mental health conditions, such as depression, psychosis and schizophrenia, which includes symptoms, causes, treatment options and the effects of medication and substance use; (2) informal caregiving, including definitions, perceptions, signs of caregiver burden, and available support services; and (3) practical skills in peer education, such as presentation techniques and an introduction of the content of the peer education sessions. The training is delivered in the Dutch language by a prevention specialist with a background in psychology, a Family Experience Expert (FEE; explained in Section 2.1 about Phase 3) and a caregiver support coach affiliated with the local caregiver support service, which has been part of TANMs coordinating organizations since 2023. The training is highly interactive and fosters a culturally sensitive approach by encouraging ambassadors to share personal experiences and explanatory models they are familiar with. A key message throughout the training is that differing perspectives on mental health conditions can coexist, and that creating space for these perspectives during the peer education sessions is essential.

After completing the training, ambassadors recruit participants for their groups and lead the intervention’s peer education sessions in the dominant language spoken within their group. This could be Dutch, but also, for example, Arabic or Turkish. Ongoing support is provided to the ambassadors in two ways, through regular feedback meetings with members of the coordinating organizations and fellow ambassadors, and through direct access to a designated contact person within the coordinating organizations who is available for individual questions, support or guidance through phone, messaging or in-person contact.

Our evaluation will focus on the current round of TANM (September 2024 – March 2025), which is co-organized by four partners, following the addition of a helpline and support service for caregivers in Rotterdam in 2023.

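### Prior acquaintance and cultural homogeneity are tested in two-way tables with no step to separate them, so overlap could give misleading quantitative support to one of them

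*Protocol article*

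**What the plan says.** Section 3.3.2 gives the questionnaire analysis the aim to "assess the potential influence of contextual factors on perceived mechanisms and outcomes". It names the contexts, "whether participants knew each other or their ambassador beforehand and the cultural homogeneity of the group", and adds "which may influence social support and group dynamics". The method is stated: "we will conduct crosstabulations of these independent and dependent variables, supplemented by chi-square tests". Nothing is said about layering the tables, stratifying, fitting both contexts together, or checking whether the contexts are related to each other.

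On size, the same section says "we estimate an effect size of 0.4" and "we expect to need around 60 completed surveys to achieve sufficient power", and expects returns "totalling approximately 80–100 questionnaires". Table 2 shows about 10 ambassadors with roughly 10 participants each.

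Section 2 describes how groups form: "ambassadors recruit participants for their groups". Ambassadors are selected partly for their access to a target community and lead sessions in the language that dominates in their group. Configuration 4a in Table 1 describes them as trusted people, well connected locally, who bring participants in.

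**The concern.** If an ambassador fills a group through his or her own network, a culturally homogeneous group will tend to be one whose members already know each other or the ambassador. A two-way table of acquaintance against, say, willingness to talk to group members then also carries any effect of shared background, and the reverse holds too. Pooled over groups, the acquaintance table also picks up whatever else differs between groups, including the ambassador. This is confounding in the contrast itself. It arises even if respondents are statistically independent, and a standard error adjusted for clustering would not by itself remove it.

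The realist question is which context sets off which mechanism. With unseparated tables, prior ties and common background may be competing explanations of the same association, and the questionnaire evidence could be credited to the wrong one.

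**Working it through.** **Inputs from the documents.** Effect size 0.4, about 60 surveys needed, 80–100 expected (section 3.3.2). Acquaintance is yes/no (Table 3), and typical answers have three levels (section 3.2.4 and Table 3), so the basic table is 2×3 with 2 degrees of freedom. There are about 10 groups (Table 2).

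**Assumptions.** The effect size is Cohen's w, because the planned test is chi-square. Two-sided alpha is 0.05 and power 0.80. Homogeneity is treated as binary. The correlation phi between acquaintance and homogeneity is not given and is varied.

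**Step 1: reproduce the plan's figure.** The noncentral chi-square with noncentrality N·w², w = 0.4 and df = 2 reaches 80% power at N = 60.2, which matches the stated 60. Other table shapes fit less well: df = 1 gives 49.1, df = 3 gives 68.1, df = 4 gives 74.6. The sample size therefore corresponds to one two-way table of one context against one answer, with nothing set aside for separating contexts.

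**Step 2: effect carried over by overlap.** Let answer Y depend only on context A, and let binary context B have no link with Y once A is known. Then P(Y=j|B=b) − P(Y=j) = [P(A=1|b) − P(A=1)] × [P(Y=j|A=1) − P(Y=j|A=0)]. Squaring, dividing by P(Y=j) and summing over b and j gives

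w(B,Y) = phi(A,B) × w(A,Y).

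With w(A,Y) = 0.4, the chance that the table for the irrelevant context is significant (df = 2) is:

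| phi | induced w | N·w² at N = 80 / 100 | significant, formula | significant, simulated | simulated, stratified by the other context |
|---|---|---|---|---|---|
| 0 | 0 | 0 / 0 | 5% / 5% | 5% / 4% | 5.0% / 4.8% |
| 0.3 | 0.12 | 1.15 / 1.44 | 15% / 17% | 16% / 18% | 4.9% / 5.2% |
| 0.5 | 0.20 | 3.20 / 4.00 | 34% / 42% | 35% / 43% | 4.6% / 4.8% |
| 0.7 | 0.28 | 6.27 / 7.84 | 60% / 71% | 61% / 73% | 5.9% / 4.9% |

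The simulation used 3,000 runs per row and N, with 10 groups (5 homogeneous), three-level answers and independent respondents.

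**Step 3: a second scenario.** Take 10 groups of 10, with 90% acquainted in five homogeneous groups and 50% or 30% in five mixed groups, and answers of 60/30/10 against 30/40/30 (all assumed). The implied overlap is phi = 0.20/√(0.7×0.3) = 0.44 or 0.30/√(0.6×0.4) = 0.61. The implied effect is w = √(0.15²/0.45 + 0.05²/0.35 + 0.10²/0.20) = 0.33. If only homogeneity matters, the pooled acquaintance test is significant in 24% to 44% of runs, against 5% when stratified by group. If only acquaintance matters, the homogeneity test is significant in 20% to 42%.

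**Step 4: cost of separating the contexts.** Scaling N approximately by 1 − phi², the N for 80% power becomes 60.2/0.91 = 66 at phi 0.3, 60.2/0.75 = 80 at phi 0.5 and 60.2/0.51 = 118 at phi 0.7. Power at N = 80 / 100 is about 87% / 94%, 80% / 88% and 62% / 73%. In the Step 3 scenario, stratifying acquaintance by group keeps (0.09 + 0.25)/(2×0.21) = 81% or (0.09 + 0.21)/(2×0.24) = 63% of the information.

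**The case against.** A reader might infer that each context will enter the program theory on the strength of its own chi-square test, so that the study will name the wrong context. The documents do not support that. Section 3.2.4 calls the questionnaire exploratory, and Table 2 gives it a supporting role in interpreting the qualitative findings. Every configuration it covers is also covered by interviews. Sections 3.3.3 to 3.4 map all sources in one matrix, look into discrepancies, refine the theory on the combined evidence and take it to a focus group. Section 4.1 disclaims causality. All of this stands and limits the consequence. It does not separate the two contexts, and a confounded table that agrees with interviews could be read as corroboration.

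Other objections also have weight:

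- Taking the tables one context at a time is an inference. Layering is not excluded, although none is named and the N of 60 fits a single two-way table.
- The overlap is assumed. Prior ties through work, training or neighbourhood can cross cultural lines, and a shared language is not a shared culture. At phi 0 there is no problem.
- An association produced wholly by the other context requires one of the two to have exactly no effect. That is a limiting case.
- Replacing the pooled test by a within-group test would discard the between-group contrast that section 3.3.2 has in mind. It could not see a group climate created by prior ties. This stands, so stratified results should be added beside the planned tables.
- If shared background leads to acquaintance, holding acquaintance fixed removes part of homogeneity's own effect. This is a reason to read layered homogeneity tables as description only.

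**Conclusion.** The point holds in limited form. Section 3.3.2 plans two-way tables and tests for two contexts that the recruitment route plausibly ties together, with no step to tell them apart. If only one context matters, at w = 0.4 and 80–100 questionnaires, the other shows a significant association in anything from the nominal 5% of studies (phi 0) to 60–71% (phi 0.7). Phi 0.3 already roughly triples the nominal rate. These figures rest on reading 0.4 as Cohen's w, on 2×3 tables, on independent respondents and on an overlap the documents do not quantify. Correlation within groups would make the tests themselves less reliable than shown.

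What is at stake is misleading quantitative support for a context within an exploratory, triangulated evaluation. The stated sample size is consistent with its own inputs and is not in question. This is a worthwhile low-cost improvement, not a flaw that undermines the study.

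**What to change.** Amend section 3.3.2 as follows:

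1. Tabulate acquaintance with participants, and acquaintance with the ambassador, against cultural homogeneity before any outcome table, and report the overlap.
2. Keep the planned two-way tables as description.
3. Add layered tables showing each context within levels of the other.
4. Add a Mantel-type test (Cochran-Mantel-Haenszel or its ordinal version) of individual acquaintance stratified by intervention group. Label it a within-group comparison that does not address acquaintance as a property of the group.
5. Report homogeneity descriptively, since it varies only between about 10 groups and cannot be separated from the ambassador.
6. State where empty or sparse cells mean the contexts cannot be separated.

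The cost is analysis wording only, with no new items or respondents. SPSS produces layered tables, and the ordinal test is available in R, which the team already uses for its power calculation. The downside is lower precision: groups in which everyone or no one was acquainted contribute nothing to the stratified test, and the loss grows with the overlap. If overlap is nearly complete, the useful result is the statement that the two contexts cannot be told apart in these data.
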